## Abstract

**Introduction:**

Empirical, observational data relating to the diagnosis, management and outcome of three common worldwide cancers requiring surgery is lacking. However, it has been demonstrated that patients in low/middle-income countries undergoing surgery for cancer are at increased risk of death and major complications postoperatively. This study aims to determine quality and outcomes in breast, gastric and colorectal cancer surgery across worldwide hospital settings.

**Methods and analysis:**

This multicentre, international prospective cohort study will be undertaken by any hospital providing emergency or elective surgical services for breast, gastric or colorectal cancer. Centres will collect observational data on consecutive patients undergoing primary emergency or elective surgery for breast, gastric or colorectal cancer during a 6-month period. The primary outcome is the incidence of mortality and major complication rate at 30 days after cancer surgery. Infrastructure and care processes in the treatment of these cancers worldwide will also be characterised.

**Ethics and dissemination:**

This project will not affect clinical practice and has been classified as clinical audit following research ethics review. The protocol will be disseminated through the international GlobalSurg network.

**Trial registration number:**

NCT03471494; Pre-results.

Strengths and limitations of this studyThis will be the first international, multicentre, prospective study to assess quality and outcomes in patients undergoing surgery for three of the most common global cancers.The collaborative methodology adopted by our group, as described elsewhere, has previously delivered two large high-quality studies, while avoiding overburdening low-resource centres that may otherwise be unable to participate in such projects.Definitions of quality in surgical cancer care are disputed and little evidence exists of their validity or appropriateness in low- and middle-income countries; high-quality data will help identify specific measures for cancer care in resource-limited settings.Only those patients undergoing primary surgery for breast, gastric or colorectal cancers will be included, and therefore outcomes in patients receiving only conservative or oncological therapy will not be included.As strict primary data monitoring is not possible within the limitations of the study, we will use a previously developed mixed-methods validation process.

## Introduction

Of the 15.2 million individuals diagnosed with cancer in 2015, 80% required surgery.^1^ In tumours amenable to surgical resection, surgery often offers the best chance of cure, particularly in early stage disease. It has been estimated that 45 million surgical procedures are needed each year worldwide, yet fewer than 25% of patients with cancer have access to safe, affordable and timely surgery. While death rates from cancer are decreasing in high-income countries, the opposite has been demonstrated in low/middle-income countries (LMICs).^2^ Up to 1.5% of the gross domestic product is lost because of cancer in some LMIC regions.^3^

Our recent LMIC-led three-stage research prioritisation exercise identified cancer surgery as a major research priority. Breast cancer, gastric cancer and colorectal cancer represent a significant burden of disease across income settings.^1 2^ Yet, most studies that examine the global distribution and outcomes of solid cancers use simulated methods due to the absence of robust data, including country-specific information on cancer epidemiology, stage distribution and treatment approaches.^1^

Our previous prospective, observational cohort studies GlobalSurg 1 and 2^4 5^ have demonstrated that patients in LMICs have an increased risk of death and complications following gastrointestinal cancer surgery. These differences persisted in multivariable models accounting for confounders in mortality (OR 3.18, 95% CI 2.12 to 4.76), major complication (OR 2.14, 95% CI 1.19 to 3.84) and SSI (OR 1.32, 95% CI 1.04 to 1.68) at 30 days after surgery. Postoperative complications can have a more severe consequences in LMICs, including death, long-term disability and catastrophic healthcare expenditure.^6^

The measures used to determine the quality of surgical cancer care are controversial and subject to ongoing debate. Guidelines produced by bodies such as the National Institute for Health and Care Excellence (UK) and American College of Surgeons in high-income countries provide some consensus.^7 8^ However, there is little evidence on the appropriateness of such guidelines in LMICs or what specific measures may indicate quality in cancer surgery in resource-poor settings.

The aim of the GlobalSurg 3 study is to determine variation in the quality of cancer surgery worldwide, focusing on patient outcomes, infrastructure and care processes. This study is driven from within our well-established global network and will be performed in upwards of 85 countries.

### Primary aims

The primary aim is to audit 30-day mortality and complication rates after cancer surgery across low-human, middle-human and high-human development index (HDI) countries.

### Secondary aims

The secondary aim is to measure the quality of surgical cancer care and is designed to be relevant in low-income, middle-income and high-income settings. Conditional data points will be dependent on the specific resources available in a hospital and will include infrastructure, care process measures and outcomes.

## Methods and analysis

This is a multicentre, international, prospective, observational cohort study of all consecutive patients undergoing surgery for breast, gastric or colorectal cancer over a 28-day period. Individual collaborators are free to choose any 28-day period within the 6-month study period to collect data. This ‘snapshot’ study design is a validated model that has been delivered successfully in previous studies.^4 5 9^

### The research collaborative

GlobalSurg (http://globalsurg.org/) is a collaboration between practising surgeons from around the world, performing research in surgery to foster local, national and international research networks. The collaborative model used has previously been described elsewhere^10^ and has already facilitated two multicentre, international, prospective cohort studies including a total of 26 228 patients undergoing emergency and elective abdominal surgery.^4 5^ The NIHR Unit on Global Surgery was established in 2017 and is a consortium between the Universities of Birmingham, Edinburgh and Warwick, together with international partners. The units objective is to advance the education of medical students and doctors in surgical science, clinical research and audit methods by promoting participation in collaborative clinical research and audit studies.

### Study setting

Any surgical unit providing emergency or elective surgery for breast, gastric or colorectal cancer worldwide is eligible to participate. An eligible hospital is not required to perform surgery for all three conditions; however, consecutive patients with breast, gastric or colorectal cancer managed surgically in an individual centre must be collected during the specified study period.

Included centres must capture all consecutive patients and ensure data collection is >90% complete. Centres with >10% missing data, when including all data points, will be excluded from the final analysis and removed from the authorship. There is no minimum number of patients per centre, as long as all eligible patients treated during the study period are included. Multiple teams covering different non-overlapping time periods at each hospital are encouraged.

### Patient inclusion and exclusion criteria

Adult patients aged 18 years or over undergoing emergency or elective surgery for breast, gastric or colorectal cancer are eligible to enter. Any operative approach or treatment intent can be used. Patients whose primary pathology is not suspected to be breast, gastric or colorectal cancer; have a recurrence of their cancer; or are undergoing a procedure that does not require a skin incision should be excluded (box 1). Each individual patient should only be included once into the study.Box 1Patient inclusion and exclusion criteriaInclusion criteriaAdult patients aged 18 years or over.Consecutive patients undergoing therapeutic surgery (curative or palliative) for breast, gastric and colorectal cancer.Patients with suspected benign pathology preoperatively whom were subsequently found to have a diagnosis of cancer following their surgery.Undergoing emergency or elective procedure requiring a skin incision performed under general or neuraxial (eg, regional, epidural or spinal) anaesthesia.Includes open, laparoscopic, laparoscopic converted and robotic cases.Exclusion criteriaOperations with a sole diagnostic or staging intent.Procedures which do not require a skin incision.Patients with recurrence of breast, gastric or colorectal cancer.

### Outcome measures

The primary outcome measure is the rate of mortality and major complication within 30 days of surgery. Major complications will be defined as occurrence of a Clavien-Dindo^11^ grade III or IV (box 2) complication within 30 days of index operation, where day of operation is day 0.Box 2Clavien-Dindo classification of major postoperative complications^11^
Clavien-Dindo grade IIIUnplanned surgical, endoscopic or radiological intervention.IIIa: intervention not under general anaesthesia.IIIb: intervention under general anaesthesia.Clavien-Dindo grade IVLife-threatening complication requiring unplanned critical care management.IVa: single organ dysfunction (including dialysis).IVb: multiorgan dysfunction.

The secondary outcomes that will be derived from this study include incidence of surgical site infection and predefined cancer-specific quality measures for infrastructure and outcomes in cancer care (box 3–5).Box 3Breast cancer quality measuresInfrastructure and care processes
*Availability and performance of:*
Preoperative fine needle aspiration/core biopsy to diagnose breast cancer.Breast/axillary MRI for staging.Breast conservation surgery for American Joint Committee on Cancer (AJCC) stage 0/I/II breast cancer.Axillary/breast radiotherapy and axillary lymph node clearance (at least 10 lymph nodes for analysis).Sentinel lymph node biopsy for early invasive breast cancer.Progesterone receptor, oestrogen receptor, human epidermal growth factor receptor 2 receptor and Ki67 status for invasive cancers.Treatment with adjuvant treatment where appropriate within 31 days of completion of surgery.Plan for radiotherapy for all with breast conserving surgery with clear margins (including ductal carcinoma in-situ [DCIS]).Treatment decisions made within multidisciplinary team meeting/tumour board.Outcomes30-day complication rate of surgical site infection, abscess formation, seroma, unplanned reoperation, unplanned readmission and requirement for unplanned critical care.Margin involvement (or ability to measure this locally) with ‘tumour on inked margin’ or a margin <2 mm in DCIS considered positive.
Box 4Gastric cancer quality measuresInfrastructure and care processes
*Availability/performance of:*
Endoscopy and biopsy to reach a diagnosis of cancer.CT chest, abdomen and pelvis scan performed for preoperative staging.Preoperative or postoperative chemotherapy for gastric cancer.Treatment decisions made within multidisciplinary team meeting/tumour board.Outcomes30-day complication rate of surgical site infection, anastomotic leak, unplanned reoperation and requirement for unplanned critical care.At least 15 regional lymph nodes removed and pathologically examined for resected gastric cancer (or ability to measure this locally).
Box 5Colorectal cancer quality measuresInfrastructure and care processes
*Availability/performance of:*
CT chest, abdomen and pelvis scan performed for preoperative staging.Preoperative MRI for rectal cancer.Planning and treatment with postoperative chemotherapy following resection for lymph node positive colon cancer.Treatment with preoperative chemotherapy/radiotherapy.Treatment decisions made within multidisciplinary team meeting/tumour board.Stoma formation rate.Outcomes30-day complication rate of surgical site infection, anastomotic leak, unplanned reoperation, unplanned readmission and requirement for unplanned critical care.Circumferential resection margin >1 mm (or ability to measure this locally).At least 12 regional lymph nodes removed and pathologically examined for resected colon cancer (or ability to measure this locally).

### Data points

Data points relating to patient characteristics, cancer staging, neoadjuvant therapy, operative treatment and postoperative period will be collected (online supplementary files 1–4). In order to maximise data completion, a minimal dataset has been designed including factors only relevant to quality and outcome measures in surgery for cancer. Review by international collaborators within the GlobalSurg Collaborative has also ensured the dataset is relevant to cancer surgery in a worldwide setting. Investigators will enter data via the secure internet-based Research Electronic Data Capture (REDCap) system.^12^ Anonymous patient data will be held on the system hosted by the University of Edinburgh, Scotland, UK.

### Investigators

The study will be undertaken by investigators around the world who will be responsible for disseminating the protocol at their individual site, ensuring appropriate study approvals are in place, identifying and including all eligible patients during each 4-week data collection period and responsible for accurate uploading of data to an online REDCap database.

A central study writing committee comprising of an internationally representative group of healthcare professionals will be responsible for data analysis, final manuscript drafting and submission. Individuals will be required to register their unit via the REDCap system and will be required to complete a training module prior to commencing data collection.

Countries with multiple sites will be assigned a country lead, who will be responsible for coordinating multiple teams across sites to ensure duplication of data does not occur. Where individual hospitals have a large number of local coordinators, a hospital lead will be appointed to aid coordination. A maximum of three local investigators can cover each 4-week data collection period, with the collection of multiple, non-overlapping collection periods by the same or different local investigators in a single centre possible. They will be responsible for gaining local audit, service evaluation or research ethics approval as appropriate to their institution.

Investigators will create clear mechanisms appropriate to their institution to identify and include all eligible patients, involving daily review of operating logbooks, multidisciplinary team meeting, admission and handover lists. This will include identifying clear pathways to accurately collect baseline, cancer-specific and follow-up data within the normal limits of follow-up. Local arrangements may include daily review of the patient and notes focused on included data points, reviewing patient status in outpatient clinics or via telephone interview at 30 days (if this is normal practice) and checking for readmission through handover lists. All investigators will be listed as collaborators on resulting publications in accordance with previous consensus guidelines for collaborative group research.^13^

### Quality of data

To ensure high data quality, a detailed protocol has been produced and published online. Translations into 12 common languages has also been performed to ease investigator understanding, including Arabic, French, Hindi, Italian, Mandarin, Portuguese, Russian, Spanish and Swahili. Collaborators are encouraged to perform data input in real-time using the REDCap system, with an individual patient record requiring to be completed before submission is possible. Data quality rules will also ensure data quality, highlighting disparities in data fields to the local collaborator for review. Online training is available to collaborators prior to the commencement of data collection at their institution, detailing secure REDCap data entry, patient outcome assessment and disease-specific parameters.

### Data validation

Data validation will be performed in two parts across a group of representative centres similar to the structure successfully used in previous studies of this nature.^5^ Case ascertainment assessment will involve an independent investigator determining the number of eligible cases within a 4-week data collection centre and comparing this to the actual number of cases submitted. By comparing samples, a quantitative estimate of case ascertainment will be produced by the central data team. Second, validators will be asked to provide data for a subset of variables, two patient variables, two operation variables and two outcome measures in order to measure data accuracy.

### Statistical analysis and power calculation

Variation across different international health settings will be tested using the HDI,^14^ a composite statistic of life expectancy, education and income indices published by the United Nations. Bayesian multilevel logistic regression models will be constructed to account for case mix, with population stratification by hospital and country of residence incorporated as random effects with constrained gradients.

Further prespecified subgroup analyses will be made by geographical country grouping, cancer-type (including the separation of colonic and rectal tumours), emergency versus elective surgery, performance status, palliative versus curative surgery, extent of staging and extent of pathological analyses. When assessing quality measures and processes similar patient groups will be compared, with potential confounding factors such as cancer-type, patient presentation, surgical intent and availability of adjuvant therapy accounted for within statistical models. Quality metrics as described earlier in the protocol will guide exploratory analysis into the global variation in surgical management and available resources. However, it is acknowledged that such guidelines, in the majority, are designed for high-income settings and therefore their attainment will not be considered mandatory or a potential definitive measure of care quality in global cancer surgery.

Data will not be analysed or reported at an individual surgeon or hospital level. Following analysis, results will be fed back to participants at the centre level, but no other centres will be identifiable.

Estimates of 30-day mortality for gastrointestinal cancer resection were determined using data from the GlobalSurg 1 and 2 studies.^4 5^ Stratification of results by HDI was performed, with prominent variation in 30-day mortality rate between high HDI and low/middle HDI groups seen after cancer surgery in both emergency surgery (11.6% [75/644] vs 27.3% [59/216]) and elective surgery (2.0% [30/1501] vs 5.5% [23/416]). An indicative sample size calculation using the smaller of these estimates suggests around 500 patients per group at 80% power (P1=0.020, P2=0.055, alpha=0.05) or 640 patients per group at 90% power would be required to conclude a difference in 30-day mortality rate between HDI groups.

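### Availability of adjuvant therapy is adjusted for as a confounder although it is itself a quality measure, so HDI comparisons of adjuvant-therapy measures lose the variation that runs through availability

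*Protocol article*

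**What the plan says.** The rule stands in the protocol article under Statistical analysis and power calculation. It opens with "When assessing quality measures and processes similar patient groups will be compared" and continues with "potential confounding factors such as cancer-type, patient presentation, surgical intent and availability of adjuvant therapy accounted for within statistical models". It states no exception for models of measures that concern adjuvant therapy. The same section names the HDI as the index for testing variation across international settings, and says that the quality metrics "will guide exploratory analysis into the global variation in surgical management and available resources".

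Under Outcome measures, the boxes list the secondary quality measures for infrastructure and care processes:

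- Box 3 (breast), under "Availability and performance of": "Treatment with adjuvant treatment where appropriate within 31 days of completion of surgery", together with radiotherapy items.
- Box 4 (gastric), under an equivalent heading: "Preoperative or postoperative chemotherapy for gastric cancer".
- Box 5 (colorectal), under the same heading as Box 4: "Planning and treatment with postoperative chemotherapy following resection for lymph node positive colon cancer". Radiotherapy appears here only as preoperative treatment.

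The Introduction gives the study aim as to "determine variation in the quality of cancer surgery worldwide, focusing on patient outcomes, infrastructure and care processes". Secondary aims adds that some data points will be conditional on the resources a hospital has.

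**The concern.** A confounder of the relation between setting and quality should be something that differs between settings without being a consequence of them, such as the mix of cancers or of elective and emergency cases. Whether a hospital can offer adjuvant therapy is a feature of its health system. It follows from the setting and determines whether patients receive the treatment. In an HDI comparison of adjuvant-therapy measures it is a mediator, and for the availability component of those measures it is the outcome itself.

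Adjusting for it changes the question from how much receipt varies between HDI groups to how much it varies among hospitals that have the therapy. A reader told that the models account for confounding would take the result as case-mix-adjusted variation in quality. A gradient produced by lack of access could then be reported as small or absent, although the Discussion says that the study will quantify global inequalities.

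**Working it through.** The protocol states no figure on this point, so there is none to reproduce. The check has two parts.

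**1. The text.** The analysis section names availability of adjuvant therapy as an adjustment factor for quality measures and processes. Boxes 3 to 5 place adjuvant or postoperative therapy under headings that cover both availability and performance. The same variable is therefore an endpoint component and a covariate.

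**2. The size, by illustration.** All rates below are assumptions.

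Inputs: availability A is 0.95 in high HDI and 0.50, 0.70 or 0.90 in low/middle HDI. Receipt given availability, R, is 0.80 in high HDI and 0.80 or 0.70 in low/middle HDI. Receipt is zero where the therapy is not available.

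Formulas:
- Total receipt: P = A × R.
- Total OR = [P_high/(1 − P_high)] / [P_low/(1 − P_low)].
- OR given availability = [R_high/(1 − R_high)] / [R_low/(1 − R_low)]. Hospitals without the therapy carry no information on the HDI effect once availability is in the model.
- Share of the log-OR removed = 1 − ln(OR given availability)/ln(total OR).

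In high HDI, P = 0.95 × 0.80 = 0.76, with odds 0.76/0.24 = 3.167.

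| A, low/middle | R, low/middle | P, low/middle | Total OR | OR given availability | log-OR removed |
|---|---|---|---|---|---|
| 0.50 | 0.80 | 0.40 | 3.167/0.667 = 4.75 | 1.00 | all |
| 0.70 | 0.80 | 0.56 | 3.167/1.273 = 2.49 | 1.00 | all |
| 0.90 | 0.80 | 0.72 | 3.167/2.571 = 1.23 | 1.00 | all |
| 0.50 | 0.70 | 0.35 | 3.167/0.538 = 5.88 | 4.000/2.333 = 1.71 | 1 − 0.539/1.772 = 70% |
| 0.70 | 0.70 | 0.49 | 3.167/0.961 = 3.30 | 1.71 | 1 − 0.539/1.193 = 55% |
| 0.90 | 0.70 | 0.63 | 3.167/1.703 = 1.86 | 1.71 | 1 − 0.539/0.621 = 13% |

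**Other quality measures.** Logistic models on expected counts were fitted with and without availability, using the same availability rates. They assumed an intercept of −0.5, a direct HDI OR of 1.5 or 2, and an OR of 1, 2 or 4 for availability. Adjustment removed between 0% (measure unrelated to availability) and 61% of the log-OR. With no direct HDI effect and an availability OR of 2 or 4, the unadjusted OR was 1.03 to 1.89 and all of it was removed.

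**The case against.** The case on the other side has four parts.

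- **Availability is studied in its own right.** The sentence after the rule plans exploratory analysis of available resources, and the Abstract says that infrastructure and care processes will be characterised. This stands: variation in availability will not go unreported. It does not restore the total HDI gradient in receipt, which no stated analysis supplies.
- **Conditioning on resources is intended.** The statement on conditional data points under Secondary aims makes performance where the resource exists a legitimate target. This stands too, but the analysis section calls the variable a confounder and does not present the result as a conditional estimate.
- **The sentence is an illustrative list.** It fixes no covariate set for each measure, and it does not itself name HDI as the exposure. If a care process were related to an outcome, availability could be a true confounder, and detailed covariate sets may be left to a fuller document. It is also fair that the protocol never says availability will enter a model of availability. However, this factor is named outright, the section tests international variation by HDI, and no exception is made for adjuvant-therapy measures.
- **The magnitude is assumed.** This is correct, and complete loss needs equal receipt given availability.

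A reader might infer that the adjustment erases the global variation the study sets out to measure, or that the secondary aim as a whole would be answered wrongly. The documents do not support this. Adjuvant therapy accounts for a few items among many in the boxes, only the variation through availability is lost, and resources are to be examined separately.

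**Conclusion.** The point holds for HDI comparisons of quality measures that concern adjuvant therapy. Followed as written, the rule over-adjusts these comparisons and yields variation given availability where the stated aim calls for variation in infrastructure and care processes. Where availability rises with HDI and promotes the measure, the gradient is understated.

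Under the assumed rates the loss is complete when receipt given availability is equal, and 13% to 70% of the log-OR when it is 80% versus 70%. It is negligible in absolute terms if availability hardly differs between HDI groups, and nil for measures unrelated to availability. The true size cannot be known from the documents.

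The primary outcome of 30-day mortality and major complications is outside this sentence. Its models are described as accounting for case mix, so nothing here bears on that result.

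**What to change.** In the analysis section, state three things:

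1. For HDI comparisons of quality measures, the main adjustment set is limited to patient case mix: cancer type, presentation and surgical intent.
2. Availability of adjuvant therapy is not adjusted for in models of measures that include adjuvant therapy.
3. For these measures the report shows availability by HDI group, unconditional receipt by HDI group, and receipt among hospitals where the therapy is available. The last is labelled as a separate conditional estimate, in line with the conditional data points under Secondary aims.

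The cost is a change of wording and a little more analysis and reporting. The plan already uses availability both as a measure and as a covariate, so no new data are implied.

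### The indicative 500 and 640 patients per HDI group are independent-patient figures; they make no allowance for the hospital and country clustering that the planned model includes, and so understate the number needed.

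*Protocol article*

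**What the plan says.** All of the power material is in the protocol article, under Statistical analysis and power calculation.

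- **Rates.** 30-day mortality comes from the network's two earlier cohorts. The smaller contrast, high versus low/middle HDI, is "elective surgery (2.0% [30/1501] vs 5.5% [23/416".
- **Calculation.** The section, calling its calculation indicative, "suggests around 500 patients per group at 80% power (P1=0.020, P2=0.055, alpha=0.05) or 640 patients per group at 90% power", as the numbers needed to show a mortality difference between HDI groups. It names no test, ICC, design effect, cluster size or number of countries.
- **Analysis.** The same section plans Bayesian multilevel logistic regression with "population stratification by hospital and country of residence incorporated as random effects with constrained gradients".
- **Exposure and scale.** Under Primary aims, the comparison is between countries grouped by HDI. The Introduction says the study "will be performed in upwards of 85 countries". Under Study setting, there is no minimum number of patients per centre, and no target total is set anywhere.

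**The concern.** The power paragraph and the model paragraph make different assumptions about the same data. The model treats patients in one hospital or country as correlated. The sample size treats every patient as independent.

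The mismatch matters more here than in many clustered designs. All patients in a country share its HDI group, so the HDI contrast lies wholly between countries and no within-country comparison helps to estimate it. Its precision depends on the number of countries and the variance between them as well as on the number of patients.

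The Discussion says recruitment will be sufficient to measure the outcomes of interest, and this paragraph holds the only numerical benchmark for that in the article. A reader who takes 500 or 640 per group as enough for 80% or 90% power under the planned model would be relying on figures that are too small.

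**Working it through.** **Inputs from the article:** P1 = 0.020, P2 = 0.055, alpha = 0.05, stated sizes 500 and 640 per group. Two-sided testing and 1:1 groups are inferred; the article does not state sidedness.

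**Step 1: reproduce the stated figures.** Exact power of the two-sided Fisher test, independent patients:

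- 80% is first reached at n = 491 per group; at 500, power is 80.8%.
- 90% is first reached at n = 635 per group; at 640, power is 90.2%.

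Other independent-patient formulas fit less well: pooled normal 462/618, unpooled 459/614, arcsine 437/585, continuity-corrected 517/674. The stated sizes are rounded Fisher values with no inflation for clustering.

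**Step 2: add clustering.** HDI is constant within a cluster, so the usual design effect applies in full:

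DE = 1 + (m − 1) × ICC, effective n = n / DE

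where m is patients per cluster. Equal cluster sizes are assumed.

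**Step 3: assumed values.** The article gives neither m nor ICC, so a range is shown. Power is the Fisher power at the effective n, and inflated size is the stated n × DE, rounded up.

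| m | ICC | DE | Effective n (500 / 640) | Power (500 / 640) | Inflated size (80% / 90%) |
|---|---|---|---|---|---|
| 10 | 0.005 | 1.045 | 478 / 612 | 78.8% / 88.8% | 523 / 669 |
| 10 | 0.02 | 1.18 | 424 / 542 | 73.2% / 84.3% | 590 / 756 |
| 20 | 0.01 | 1.19 | 420 / 538 | 72.7% / 84.0% | 595 / 762 |
| 20 | 0.02 | 1.38 | 362 / 464 | 65.5% / 77.4% | 690 / 884 |
| 20 | 0.05 | 1.95 | 256 / 328 | 47.5% / 60.5% | 975 / 1248 |

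For example, with m = 20 and ICC = 0.01: DE = 1 + 19 × 0.01 = 1.19; 500 / 1.19 = 420; 500 × 1.19 = 595; 640 × 1.19 = 761.6, rounded up to 762.

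**Step 4: how much room the rounding leaves.** The stated sizes still meet their stated power while DE is at most 500/491 = 1.018 (80%) or 640/635 = 1.008 (90%). With clusters of 10 these limits correspond to an ICC of about 0.018/9 = 0.002 and 0.008/9 = 0.0009. Beyond that, power is below the stated level.

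**The case against.** **The figures are indicative.** The strongest objection is that the article states no power for the study as a whole. It offers a rough minimum. Recruitment is by consecutive enrolment at any eligible hospital, across 85 or more countries, and the two earlier cohorts together had 26 228 patients. A reader might infer from the missing design effect that the study is underpowered, and the documents do not support that. With an assumed 1,000 patients per group over 28 countries per group and ICC 0.01, m = 35.7, DE = 1.347, effective n = 742 and Fisher power is about 94%. This objection stands against any claim about the final study. It does not rescue 500 and 640 as the numbers required.

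**The size of the loss is assumed.** This is correct. With clusters of 10 and ICC 0.005 the loss is about 2 points. If 85 countries split evenly over two groups (42.5 each, also assumed), then at n = 500, m = 11.8, DE = 1.11 at ICC 0.01 and power is about 76%. Only the direction is certain. The design effect is also an approximation to the planned model, and case-mix adjustment could offset the loss or add to it.

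**The arithmetic is right.** It is, for independent patients. The fault lies in the assumption.

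**The analysis already models clustering, and an article condenses.** Intervals for the HDI effect should indeed reflect clustering, so no estimate is at risk. Detail on variance components could sit in the full protocol. But the article prints a size, a power and the inputs, and those printed figures do not match the model printed beside them.

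**Conclusion.** The point holds as a moderate sample-size assumption problem. The figures 500 and 640 per HDI group answer a question about independent patients, while the planned analysis compares countries with hospital and country random effects. Apart from the small slack left by rounding, a positive ICC puts their power below 80% and 90% and makes them understate the number needed.

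Over the assumed range (clusters of 10 to 20, ICC 0.005 to 0.05), power runs from about 79% down to 47.5% at 500 and from about 89% down to 60.5% at 640. These values illustrate the range and are not estimates for this study. Whether the completed study has adequate power cannot be determined from the article in either direction.

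**What to change.** In the power paragraph:

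1. Label 500 and 640 as effective, independent-patient numbers per group, and name the test used.
2. Restate the size or the power after inflation by 1 + (m − 1) × ICC, or by simulation from the planned multilevel model. Take country and hospital variance from the GlobalSurg 1 and 2 data that supplied P1 and P2.
3. Give the assumed number of countries per HDI group and patients per country beside the number of patients, because the contrast is between countries.

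The cost is one rewritten paragraph and a short calculation on data already held. The stated figure will look less favourable. Enrolment, conduct and the planned model do not change.
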